##### Cambodia:

Sihanouk Hospital Center of Hope is a non-governmental hospital located in Phnom Penh providing low cost medical care for the poor and disadvantaged. They have a general outpatient primary healthcare clinic, which will be the recruitment site for this study. Per day, approximately 175 patients visit the outpatient clinic and the estimated HCV prevalence is 5%.

All individuals visiting the outpatient clinic will be offered to participate in the study, until enrolment targets for HCV negative participants are reached (see Table 5 for enrolment targets). Once these targets are reached, only individuals with known positive HCV status will be enrolled in the study. From the beginning of enrolment, known HCV positive individuals registered in the outpatient clinic database, will be contacted and invited to participate in the study (see also section 4.3.2 Potential bias). Travel of these patients will be reimbursed according to local inner-city public transport fares.

The outpatient clinic is located in close proximity to the reference laboratory, allowing daily transport of samples from the clinic to the laboratory.

### **3.4.2 Eligibility criteria**

Individuals are eligible to participate in the study if all of the following criteria apply:

- $\geq 18$  years of age
- Known or unknown HCV serology
- No history of past or present HCV treatment
- Willing to undergo the information and consenting procedure and subsequently have enough time to participate in the study
- Willing to provide 13 ml venepuncture blood sample and a minimum of four whole blood fingerstick samples
- Willing to perform an HIV test
- Individuals can already be registered at the local site or register for the first time when enrolling in the study

Note: Prospective approval of protocol deviations to recruitment and enrolment criteria, also known as protocol waivers or exemptions, is not permitted.

### **3.4.3 Exclusion criteria**

Participants are excluded from the study if any of the following exclusion criteria apply:

- Not able to consent themselves

### **3.4.4 Screen failures**

Screen failures are defined as participants who consent to participate in the clinical study but are not subsequently undergoing any or all study procedures. Participants who do not meet the criteria for participation in the study (screen failure) may be rescreened.

A screen failure for this study would be a participant who agreed to provide a venepuncture blood sample but from whom it was subsequently not possible to obtain this sample due to difficult venous access or needle phobia.

Furthermore, a participant is classified as screen failure if information provided is subsequently discovered to be incorrect (e.g. false medical history).

## **4 Study intervention**

Study intervention is defined as any investigational intervention(s), marketed product(s), or medical device(s) intended to be used with a study participant according to the study protocol.

This diagnostic accuracy study aims to evaluate performance of HCV RDTs independently of the routinely used HCV RDTs at the study sites. Test results of the study RDTs or final results of this study will not influence standard medical care provided at the site.

#### 4.1 Investigational product (or Study intervention)

The investigational products (index tests) used in this study and key operational characteristics are listed in Table 3. All tests detect antibodies to HCV antigens.

**Table 3:** *Investigational products and key operational characteristics*

|                                           | Wantai                                                               | PMC                      | AccessBio                |
|-------------------------------------------|-----------------------------------------------------------------------------|---------------------------------|---------------------------------|
| Sample types                       | Whole blood, serum, EDTA plasma                                             | Whole blood, serum, EDTA plasma | Whole blood, serum, EDTA plasma |
| Intended users                     | Professional use                                                            | Professional use                | Professional use                |
| Whole blood sample volume          | One drop                                                                    | One drop                        | One drop                        |
| Application method                        | Provided pipette                                                            | Provided pipette                | Provided pipette                |
| Plasma/serum sample volume         | 50 µl                                                                       | 35 µl                           | 10 µl                           |
| Application method                        | Provided pipette                                                            | Provided pipette                | Provided pipette                |
| Buffer requirements                | 1 drop                                                                      | 1 drop                          | 2 drops                         |
| Incubation time                    | 10 min                                                                      | 20 min                          | 15 min                          |
| Result stability time              | 5 min                                                                       | 10 min                          | 10 min                          |
| Plasma/serum 4°C storage stability | 3 days                                                                      | 3 days                          | 3 days                          |
| Kit storage conditions             | 2-30°C                                                                      | 2-30°C                          | 2-30°C                          |
| Total test time                    | 15 min (negatives need re-checking at the end of the result stability time) | 20 min                          | 25 min                          |

Other diagnostic tests (comparator, reference and confirmatory tests) provided for use in this study are:

- “WHO PQed RDT” Abbott SD Bioline HCV Test
- EIA 1: Diasorin Murex Anti-HCV 4.0
- EIA 2: Fujirebio INNOTEST HCV Ab IV
- LIA: Fujirebio INNO-LIA HCV Score
- HCV RNA assay (Abbott RealTime HCV assay for RNA PCR in Georgia; CE-IVD marked HCV RNA assay in Cambodia)
- HCV genotyping assay (Abbott RealTime HCV Genotype II assay in Georgia; Siemens Versant HCV genotype 2.0 in Cambodia - tbd)

Instructions for use of the investigational product(s) are provided separately from this protocol.

Medical device incidents, including those resulting from malfunctions of the device (or IVD), must be detected, documented and reported by the investigator at each site throughout the study (see section 7.1 and Appendix 2)

## **4.2 Preparation/Handling/Storage/Accountability**

### **4.2.1 Acquisition**

Procurement of the investigational products will be done through FIND, who will coordinate shipments from the manufacturer. It is the responsibility of each study site to maintain an updated inventory of the study materials and to inform FIND immediately if additional materials are required.

The investigator or designee must confirm appropriate temperature conditions have been maintained during transit for the investigational product received and any discrepancies are reported and resolved before its use.

### **4.2.2 Storage**

Procedures for product storage and disposal will be described in the study manual.

The investigational product must be stored in a secure, environmentally controlled, and monitored (manual or automated) area in accordance with the labelled storage conditions, and access must be limited to the investigator and authorized site staff.

### **4.2.3 Test handling and performance**

Testing using the investigational products will be performed according to the manufacturer's instructions outlined in the study manual.

Only blood samples from participants enrolled in the study will be processed with the investigational product and only authorized site staff will be responsible for processing.

### **4.2.4 Accountability**

The investigator is responsible for investigational product accountability, reconciliation, and record maintenance (i.e., receipt, reconciliation, and final disposition records). Investigational Product Accountability logs filled at each site will ensure the proper follow-up of the used, failed and remaining investigational products.

Further guidance and information for the final disposition of unused investigational product are provided in the study manual.

### **4.2.5 Export and import permits**

It is expected that most countries will require import permits to receive the investigational materials. Local sites will be responsible for making import permit applications in a timely manner.

### **4.2.6 Quality control check for incoming shipments**

Upon arrival of each new shipment of assays, the sites will conduct and document an incoming quality check following the study manual. New lots may only be used after this quality check is successfully passed.

#### **4.2.7 Local procurement**

Sites are responsible for assessing their needs and procuring any supplies, reagents and kits needed for the study that are locally available in order to include these costs in the study budget.

### **4.3 Minimisation of error and bias**

#### **4.3.1 Potential errors**

There is a risk of procedural error when performing four different RDTs consecutively by one operator, as each test has slightly different procedures. This risk will be minimized by training the staff on the different RDT procedures as well as on how to process all four RDTs consecutively. Furthermore, the order of the investigational RDTs will be determined based on the required incubation time to ensure timings can be adhered to. The training will be performed on known HCV antibody negative and positive samples (de-identified samples provided by the reference laboratories), as well as fingerstick blood (procedural training only).

For each RDT, training on results reading will be conducted based on manufacturer-provided RDTs with bands of different intensities. If these cannot be provided by the manufacturers, training will be conducted on serial dilutions of known HCV antibody positive control samples.

All study samples and aliquots will be coded with unique FIND identifiers on pre-printed labels, to minimize the risk of sample mix-up due to mistakes in manual labelling

#### **4.3.2 Potential bias**

Participants will be enrolled sequentially as they present to the healthcare facility. Eligibility screening and consenting will be done by a person other than the healthcare professional who performs the test to avoid bias in RDT reading in case of a known HCV status. Patients with known HCV serology status will be instructed not to share this status with the HCV RDT tester.

Once the set enrolment targets for HCV negative individuals is reached, only individuals with known HCV-positive status will continue be enrolled in the study to meet required enrolment targets for HCV positive individuals. There is a risk to introduce bias in RDT interpretation, if all enrolled patients are known to be HCV positive. To minimise this risk, known HCV positive patients will be contacted and invited to participate in the study from the beginning of recruitment, to present to the facilities in the same timeframe as individuals of unknown, and thus often negative, HCV status.

The SD Bioline HCV RDT (WHO PQed) will be performed after the performance of the index tests to avoid interpretation bias by the reader based on the results of the WHO PQ-approved test.

EDTA plasma and serum samples will be tested freshly on all RDTs on the same day of sample collection to avoid difference in sample age compared to fingerstick whole blood from the same participant and between samples from different participants.

All reference tests will also be performed on fresh EDTA plasma samples within the allowed sample stability timeframe at 4°C (as per manufacturer's IFU).

The laboratory technicians who perform reference testing, will not have access to the RDT results at the time of testing, as they will not require access to Open Clinica, where RDT results are

entered. This will minimize bias in LIA result interpretation, which is based on visual line intensity scoring. There is no bias in EIA result interpretation, as it is based on electronic read-outs (see section 10.2 Data management).

There is a risk of bias in LIA interpretation due to visual interpretation. This will be addressed by the scoring of all blots by two independent readers and joint discussion in case of discrepant interpretations. In case the two readers cannot agree, a third reader will be asked to score the results independently.

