## **3.2 Scientific rationale for study design**

Both study sites are located in resource-limited settings, which is the intended use setting for HCV RDTs to be pre-qualified by the WHO [3]. RDT testing will be performed by intended users of the tests, i.e. primary healthcare workers who routinely perform blood sampling procedures on patients, but are not experienced in performing sophisticated diagnostic laboratory testing.

Matched fingerstick whole blood, EDTA plasma and serum sample will be assessed to evaluate the performance in all sample types claimed by the RDT manufacturers. Performance of RDTs in these sample types will be compared to a composite reference standard as well as to an HCV RDT already pre-qualified by WHO (SD Bioline).

The use of a composite reference standard designed of two EIAs and one LIA, allows accurate characterisation of HCV antibody status (see section 6. Study Procedure for further detail). This method is also used by WHO PQ for sample characterisation during independent laboratory evaluations of RDTs [17]. Using a WHO-PQed HCV RDT (SD Bioline) will allow direct performance comparison in all sample types in the intended use setting.

Assessment of HCV viral load will provide additional information on the status of the infection of the patient, i.e. active or resolved. This information will be used to support the interpretation of discordant results, as some RDTs can have lower sensitivity in patients with resolved HCV infection [18].

Genotyping of HCV positive samples will allow to assess RDT performance in relation to different HCV genotypes. Study sites were chosen to ensure genotype diversity; the most prevalent genotypes in Georgia and Cambodia are 1b, 2, 3 and 1b, 6, respectively [11-13].

Testing study participants for HIV will provide important additional information, as some RDTs have shown lower performance in patients co-infected with HIV during the previous FIND HCV RDT study [4]. Furthermore, it is known that immunocompromised patients may have lower HCV antibody titres [19, 20], potentially impacting RDT performance.

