## 6.2 RDT testing

### 6.2.1 Fingerstick blood

Fingerstick blood will be collected according to each manufacturer's IFU, e.g. with a provided pipette or capillary. All RDTs for a single participant will be performed by the same operator, who is a trained healthcare worker at the facility. The three selected study RDTs have an incubation time of 10-20 min prior to result readiness, which will allow for all RDTs to be started consecutively and read more or less simultaneously, once the incubation time is over and within the allowed reading time frame (see Table 3).

Results of the study RDTs will be read before results of the WHO PQed RDT and all results will be recorded by the operator into the Participant Worksheet.

Any invalid RDT runs will be repeated immediately, using a fresh drop of fingerstick blood, EDTA plasma or serum.

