### **6.6.3 Discordant results**

Discordant results of the study RDTs to the WHO PQed RDT (SD Bioline) will be repeated for EDTA plasma and serum samples only, as the participant may not be available for repeat testing of fingerstick whole blood. Discordant results will be repeated in duplicate within 24h at the primary healthcare facility, using the same lot.

Performance analysis will be conducted using initial results only. The results of further testing of samples with discrepant results will be reported separately as additional information about RDT performance.

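### SD Bioline, the reference for secondary outcome 2.1, is read last by the operator who has just read the three study RDTs, so its reading is not blind and may be pulled towards agreement

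*Protocol*

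**What the plan says.** Section 4.3.2 fixes the order and gives its only reason: "The SD Bioline HCV RDT (WHO PQed) will be performed after the performance of the index tests to avoid interpretation bias by the reader". The sentence names no specimen type. Section 4.3.1, also without limiting the specimen, describes one operator performing the four RDTs in succession.

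Section 6.2.1, under a fingerstick heading, adds:
- "All RDTs for a single participant will be performed by the same operator, who is a trained healthcare worker at the facility"
- the incubation times allow "all RDTs to be started consecutively and read more or less simultaneously"
- "Results of the study RDTs will be read before results of the WHO PQed RDT and all results will be recorded by the operator"

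Section 8.4.1 makes SD Bioline the reference standard for outcome 2.1. Section 3.2 gives it a second role: "Using a WHO-PQed HCV RDT (SD Bioline) will allow direct performance comparison in all sample types in the intended use setting".

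On disagreement between a study RDT and SD Bioline, section 6.6.3 says "Discordant results of the study RDTs to the WHO PQed RDT (SD Bioline) will be repeated for EDTA plasma and serum samples only" and "Discordant results will be repeated in duplicate within 24h at the primary healthcare facility, using the same lot". It then says "Performance analysis will be conducted using initial results only".

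The blinding described in 4.3.2 covers the laboratory technicians who run the EIAs and the LIA. They cannot see RDT results, and the LIA has two independent readers. Nothing comparable is described for the SD Bioline reader.

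**The concern.** The protocol accepts that knowing one RDT result can bias the reading of another; that is why SD Bioline comes last. It applies the argument in one direction only. An RDT line is judged by eye, and section 4.3.1 plans training on bands of different intensity. When the operator reaches a faint SD Bioline line, three results for the same specimen are already known.

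In a diagnostic accuracy analysis, the reference should be read without knowledge of the index test. For outcome 2.1 that condition is not met. If borderline SD Bioline readings lean towards what the study RDTs showed, agreement is overstated: sensitivity, specificity, predictive values and kappa against SD Bioline all look better than they would with an independent reading. The direct comparison promised in 3.2 is also weakened, because the comparator's recorded result is no longer independent of the tests it is compared with.

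In plasma and serum there is a second, weaker pressure. A discordant first reading creates duplicate repeat work at the facility within a day; an agreeing one does not. A discordance that is read away is never repeated or reported under 6.6.3, and it goes into the 2.1 estimates as it stands.

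**Working it through.** **Side by side.**

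| Feature | EIA/LIA composite (outcome 1.1) | SD Bioline (outcome 2.1) |
|---|---|---|
| Who reads | Reference laboratory technicians | Operator who has read the study RDTs |
| Index results known at reading | No | Yes |
| Second reader for a visual result | Yes, for the LIA | None described |
| Repeat triggered by disagreement with a study RDT | None described | Yes, plasma and serum only |

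**The plan's own figures.** Table 4 is reproduced by n = (z0.975 + z0.80)² p(1−p) / 0.05², taking a two-sided 5% level as an assumption. p = 0.90 gives 282.6, so 283; p = 0.95 gives 149.1, so 150. These figures do not bear on the reading order, and no sample size changes.

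**Illustration of the size.** The documents give neither the accuracy of SD Bioline nor a rate of influenced readings. The assumptions are:
- 440 antibody-positive and 1,100 antibody-negative participants (Table 4).
- All four tests have equal accuracy: 90%/90% or 95%/95% (section 8.2), or 96.3%/98.3% (previous-study averages, synopsis).
- Errors are independent given true status.
- When SD Bioline differs from the majority of the three study RDTs, its call switches to that majority with probability f.

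The recorded SD Bioline call then equals the unbiased call with probability 1−f and the index majority with probability f.

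*At 95%/95%, antibody positives.* The majority is positive with probability 0.95³ + 3(0.95²)(0.05) = 0.99275. A given study RDT and the majority are both positive with probability 0.95(1 − 0.05²) = 0.947625. Positive agreement is

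[(1−f)(0.9025) + f(0.947625)] / [(1−f)(0.95) + f(0.99275)],

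which is 95.0%, 95.05%, 95.1% and 95.2% at f = 0, 0.10, 0.25 and 0.50. Among true positives alone the effect is very small.

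*Adding the antibody negatives.* The majority is falsely positive with probability 3(0.05²)(0.95) + 0.05³ = 0.00725. It is positive together with a given study RDT with probability 0.05(1 − 0.95²) = 0.004875.
- f = 0: (440×0.9025 + 1,100×0.0025) / (440×0.95 + 1,100×0.05) = 399.85/473 = 84.5%.
- f = 0.50: numerator 0.5×399.85 + 0.5×(440×0.947625 + 1,100×0.004875) = 411.1; denominator 0.5×473 + 0.5×(440×0.99275 + 1,100×0.00725) = 458.9; ratio 89.6%.

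Most of the movement comes from SD Bioline false positives being read away: 55 at f = 0, and 0.5×55 + 0.5×7.975 = 31.5 at f = 0.50.

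Apparent sensitivity against SD Bioline (kappa in brackets):

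| Assumed sens/spec | f = 0 | f = 0.10 | f = 0.25 | f = 0.50 |
|---|---|---|---|---|
| 90%/90% | 72.6% (0.592) | 74.2% (0.612) | 76.7% (0.641) | 80.9% (0.690) |
| 95%/95% | 84.5% (0.777) | 85.5% (0.788) | 87.0% (0.804) | 89.6% (0.831) |
| 96.3%/98.3% | 92.3% (0.892) | 92.7% (0.897) | 93.3% (0.905) | 94.4% (0.919) |

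The rise is 0.4 points (92.3 to 92.7) at the smallest and 8.3 points (72.6 to 80.9) at the largest. Kappa rises by 0.005 to 0.098.

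**The case against.** The order has a stated and sensible purpose. The study RDTs are the products under evaluation, and protecting their readings is the first priority. Outcome 2.1 is secondary. Operational detail is left to a study manual that is not at hand. All of that stands, and it limits the weight of the point.

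Several stronger readings are tempting but not supported:

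- *A reader might infer that every discordant call costs the operator repeat work.* Section 6.6.3 exempts fingerstick blood and says where repeats are done, not by whom. The same-operator sentence is most explicit for fingerstick blood, where there are no repeats. And if the three study RDTs disagree among themselves, no SD Bioline reading avoids a repeat.
- *A reader might infer that index results are already written down when SD Bioline is read.* Section 6.2.1 says only that they are read first, with all readings close together. Knowledge at the time of reading is enough for the concern.
- *A reader might infer that study RDT errors are hidden.* Every participant's EDTA plasma is tested by both EIAs and the LIA. Errors are counted against that composite in outcome 1.1 whatever SD Bioline shows, apart from the samples Table 8 excludes.
- *A reader might model drift towards one study RDT at a time and obtain a clear rise in agreement among positives.* The operator sees three results. At 95% with independent errors, one study RDT misses while SD Bioline detects in 440×0.05×0.95 = 20.9 positives. In 20.9×0.95² = 18.9 of these the other two study RDTs are positive, so drifting to the lone negative would go against the majority.

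What remains is that the SD Bioline reading is not blind to the index results and section 4.3.2 does not say so.

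**Conclusion.** The point holds for secondary outcome 2.1 and for comparisons between the study RDTs and SD Bioline. The fixed order with one operator guards against bias in one direction and leaves the reference for a named outcome open to it in the other. The supportable wording is that the SD Bioline reading may be pulled towards agreement; the documents do not show that it is. The workload incentive is possible for plasma and serum only, at the level of the facility. Primary outcome 1.1 is untouched.

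The size cannot be derived from the documents. The 0.4 to 8.3 point range rests on an assumed SD Bioline accuracy, independent errors, drift to the index majority and an assumed f. It shows direction and sensitivity to assumptions and is not a forecast. This is a limitation of a secondary outcome, worth correcting because correction is cheap.

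**What to change.** 1. **Plasma and serum.** After the study RDTs have been read, run SD Bioline the same day as a separate batch of coded aliquots, recorded on a sheet that does not carry the index results. Aliquots are already coded (4.3.1) and same-day testing is already required (4.3.2), so the index readings stay protected.
2. **Section 6.6.3.** Have a staff member other than the reader, such as the existing consent and eligibility person, compare the sheets each day and trigger the duplicate repeats within the existing 24-hour window.
3. **Fingerstick blood.** Record SD Bioline on a separate sheet. Full blinding is not achievable with one operator and near-simultaneous reading. Turning cassettes face down would not remove memory and would clash with the re-check of Wantai negatives noted in Table 3.
4. **Section 4.3.2.** State that the order protects the study RDT readings only, that the fingerstick SD Bioline reading is not fully blind to them, and that this limits outcome 2.1 and the direct comparison for whole blood.

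Cost: protocol and worksheet wording, slightly more handling and a daily sheet comparison by existing staff. No additional participants or tests are needed.

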|                                                       | Day 1                                                        | Collection of venepuncture blood in EDTA plasma and serum tubes                  |                                             |                                                              |
| Testing procedures without participant present | Day 1                                                        | Centrifugation and separation of EDTA plasma and serum                           | Days 2-7                                    | HCV and HIV RNA confirmatory testing of RDT-positive samples |
|                                                       | Day 1                                                        | Preparation of EDTA plasma and serum aliquots                                    | Days 2-7                                    | EDTA plasma EIA/LIA reference testing                        |
|                                                       | Day 1                                                        | EDTA plasma and serum testing on three study HCV RDTs and one WHO-PQ RDT         |                                             |                                                              |
| Data entry                                     | Day 1-7                                                      | Transcription of Participant Worksheet information and results into Open Clinica |                                             |                                                              |

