## 6.1 Participant enrolment

Enrolment will be done at primary healthcare facilities by trained staff.

All individuals attending the healthcare facilities for any health-related issue will be invited to participate in the study.

Individuals will be screened for eligibility and must provide their written consent to participate. After obtaining the signed consent, a participant ID is assigned to him/her and the participant is recorded in the enrolment log.

A participant who is not yet registered at the local healthcare facility, will be entered into care through the locally required registration procedure.

At enrolment, the following information will be collected for each participant, based on verbal information provided by the individual:

- Age
- Gender
- HCV status (known/unknown)
- Medications taken (including antiretrovirals)
- Recent vaccination (within the last 12 months)
- Concomitant infections (including HIV and approximate date of last negative HIV test, if applicable)

After recording the participant's demographic and clinical data in the dedicated Participant Worksheet, blood samples can be collected to perform all necessary study testing.

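### The workflow does not secure the blinding in section 4.3.2: the RDT operator writes on the worksheet that holds HCV status, and in Georgia RDT-triggered PCR shares a laboratory and a week with the visually scored LIA

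*Protocol*

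**What the plan says.** **RDT reader.** Section 4.3.2 sets two safeguards. The first is: "Eligibility screening and consenting will be done by a person other than the healthcare professional who performs the test". Its purpose is given as "to avoid bias in RDT reading in case of a known HCV status". The second is: "Patients with known HCV serology status will be instructed not to share this status with the HCV RDT tester".

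Section 6.1 lists the items collected at enrolment, among them HCV status (as known or unknown), medications and concomitant infections. These are entered as "demographic and clinical data in the dedicated Participant Worksheet" before any blood is collected. Section 6.2.1 then says that "all results will be recorded by the operator into the Participant Worksheet", and section 3.1.1 names the same form for the RDT results. No masked page or separate results form is described.

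**Reference reader.** Section 4.3.2 promises: "The laboratory technicians who perform reference testing, will not have access to the RDT results at the time of testing". The only mechanism given is that these technicians do not need Open Clinica. LIA blots are scored by two independent readers, with a third if they cannot agree.

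Table 1 schedules "HCV and HIV RNA confirmatory testing of RDT-positive samples" on days 2-7, the window it also gives for EIA and LIA. Under section 3.1.3, any initially reactive RDT result triggers HCV PCR. In Georgia this is done at the Lugar Centre, which is also the reference laboratory. In Cambodia it is outsourced to another institute (sections 3.1 and 3.1.3).

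**The concern.** The RDTs and the LIA are both read by eye, so weak lines are where prior knowledge can act.

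For the RDT, the patient is told to stay silent while the form in the operator's hands carries a closely related cue. Known positives are actively invited at two sites, and once the negative targets are met they are the only people enrolled there (sections 3.4.1 and 4.3.2). Section 4.3.2 itself describes people of unknown status as often negative.

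For the LIA, a PCR request tells whoever sees it that at least one RDT was reactive. The LIA result decides every sample on which the two EIAs disagree. Where the EIAs agree, a contrary or indeterminate LIA removes the sample from the main analysis (Table 8). An RDT-negative, EIA-positive sample scored LIA-negative or indeterminate would thus drop out of the sensitivity denominator and take a false negative with it.

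The data are meant to support WHO pre-qualification or CE-marking. Section 1.1 cites a 98% sensitivity requirement and earlier sensitivities of 95.9% to 97.1%. The distances are 98 - 97.1 = 0.9 and 98 - 95.9 = 2.1 points, so a small reading bias would matter.

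**Working it through.** There is no stated figure to reproduce. The check traces who sees what, then sizes each route from Table 5.

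**1. Worksheet route.** HCV status is entered in the Participant Worksheet at enrolment (6.1). Blood is then collected, and the operator enters RDT results in the Participant Worksheet (3.1.1, 6.2.1). Separating the enroller from the tester blocks what is said between people, not what stands on the form.

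**2. How strong a cue is known?** Inputs from Table 5:

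| Site | Prevalence | Target positive | Target negative |
|---|---|---|---|
| Georgia OST | 40% | 310 | 140 |
| Georgia NCDC | 5% | 20 | 300 |
| Cambodia SHCH | 5% | 110 | 660 |

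Walk-in positives expected while the negative target fills = negatives × prevalence / (1 - prevalence).

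- OST: 140 × 0.40 / 0.60 = 93, leaving 310 - 93 = 217.
- SHCH: 660 × 0.05 / 0.95 = 35, leaving 110 - 35 = 75.
- Known positives needed: 217 + 75 = 292, and 292 / 440 = 66%.

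NCDC invites no known positives, so it adds nothing here. Walk-ins may also know their status, so the share recorded as known could be higher.

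**3. Direction.** If faint lines are called positive more readily in people marked known, sensitivity rises. Among reference-negative people marked known, the same habit lowers specificity. If faint lines in people marked unknown are called negative, specificity rises. The net effect on specificity is therefore open.

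**4. Size, as illustration only.** The protocol gives no rate of faint lines. Assuming that the cue converts 1 to 2 results per 100 known positives from negative to positive, pooled sensitivity moves by 0.66 × 1 to 0.66 × 2 = about 0.7 to 1.3 points.

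**5. PCR route, Georgia.** Georgia supplies 310 + 20 = 330 of 440 target positives (75%), 140 + 300 = 440 of 1,100 target negatives (40%) and 770 of 1,540 participants (50%). Before any request, the chance that a Georgian sample is positive is 330 / 770 = 43%.

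Let s be the share of positives with at least one reactive RDT (assumed 0.90 to 1.00) and f the share of negatives with at least one. Then P(positive | request) = 330s / (330s + 440f). There are 4 RDTs × 3 specimen types = 12 results per participant.

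- False reactives fully coincide, specificity 95% to 98.3%: f = 0.05 to 0.017, giving 93% to 98%.
- False reactives independent, specificity 98.3%: f = 1 - 0.983^12 = 0.186, giving 78% to 80%.
- False reactives independent, specificity 90% in whole blood and 95% otherwise: f = 1 - 0.90^4 × 0.95^8 = 0.565, giving 54% to 57%.

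The absence of a request is informative too: P(negative | no request) = 440(1 - f) / [440(1 - f) + 330(1 - s)], about 85% to 100% over these cases.

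**6. What protects the LIA reader?** Lack of Open Clinica access hides the recorded RDT results. It does not hide which samples are sent for PCR. Two independent readers reduce individual reading error, but both may have the same knowledge.

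**The case against.** A reader might infer that the blinding is undone, that in both countries the LIA readers hold a list of RDT-positive samples, and that sensitivity and specificity are both inflated beyond repair. The documents do not support that reading.

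- The worksheet field is known or unknown, not positive or negative, and some people marked known may be known negatives. The form is not shown, nor are Figures 2 and 3, and section 10.1 leaves the source-data definition to be refined at site initiation. A shared form name does not prove a shared page. Medications add little, because past or present HCV treatment is an exclusion.
- The protocol names no PCR list, does not say that LIA readers handle PCR requests, and fixes no order between PCR and LIA.
- Sharing a laboratory is documented for Georgia only. Section 6.4 sends Cambodian samples to the reference laboratory first, so staff there might learn which aliquots to forward, but that is inference.
- A request does not reveal the RDT result. It shows that at least one of 12 results was reactive, without naming the test or specimen.
- Where the EIAs agree, the LIA can exclude a sample but cannot reverse its status.
- The RDT limb can be examined in analysis, because known or unknown status is collected.

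All of this stands, and it limits the claim. It does not remove it. Section 4.3.2 names its safeguards explicitly, and neither route is covered by them. Followed as written, the workflow puts the status field and the RDT results on one named form.

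**Conclusion.** The blinding in section 4.3.2 is not secured by the protocol's own workflow.

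The RDT limb is the firmer one. About 292 of 440 positives (66%) would have to be known positives, if the Table 5 prevalences hold and the shortfall is met as planned. Known is then a strong cue at the OST and SHCH sites. It could inflate sensitivity, by an amount the documents cannot give; the 0.7 to 1.3 points rest wholly on an assumed conversion rate. The effect on specificity could go either way.

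The LIA limb holds for Georgia, with 75% of target positives and half of participants, and is only a possibility in Cambodia. No magnitude can be given, since the number of samples whose LIA score is open to judgement is not stated.

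This should be put right before enrolment. It is a gap in the stated safeguards, not evidence that bias will occur.

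**What to change.** **RDT reader.** In sections 6.1, 3.1.1 and 6.2.1, split the worksheet. Status, medications and co-infections go on an enrolment form kept by the enroller. The operator receives a results-only form with the participant ID. HIV testing depends on recorded HIV status (3.1.1, 6.9), so if the same operator runs the HIV RDT, the enroller adds only whether it is to be run.

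Report sensitivity by known versus unknown status as a check. It is a coarse one: with about 292 and 148 positives and 95% sensitivity, the half-width for the difference is 1.96 × √[0.95 × 0.05 × (1/292 + 1/148)] = 4.3 points. The groups also differ in site mix. It supplements the form change and cannot replace it.

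**LIA reader.** In section 4.3.2, state for both countries either that EIA and LIA scores for a sample are recorded and locked before RDT-triggered PCR requests are visible to the LIA readers, or that existing staff who do not score LIA handle those requests. The second option leaves the timing of confirmatory testing untouched.

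**Cost.** A form redesign before first enrolment, a short addition to section 4.3.2 and the laboratory manual, and slightly more sample handling.
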